### Training of NRU nurses

Five Moyo NRU nurses were trained to conduct the Kusamala Program. Prior to the training they were given a test based on the Food and Agriculture Organization *Guidelines for assessing nutrition-related knowledge, attitudes and practices* to determine their baseline understanding [31]. Questions from the following modules were used: feeding young children (6–23 months), malnutrition, personal hygiene, water and sanitation, and food-based dietary guidelines [31]. Mean scores out of a possible 25 points were 21.8 ± 0.8, indicating that nurses already had familiarity of nutrition and WASH components as expected considering their work in the NRU. Nurses then received training for a duration of 6 hours and, over the next 2 weeks following training, the nurses practiced at least two sessions with primary caregivers and children in the ward. Nurses were then given the same test; mean scores were 24.2 ± 1.3. Differences between the pre-test and post-test were significantly different, showing an improvement in mean scores of 2.4 points (*p* = 0.02). Refresher training of NRU nurses will be conducted bi-annually. In addition, nurses received training in care for child development.

### Primary outcome

The primary outcome is child development 6 months after discharge (*t*
_*6*_). Child development will be assessed with the MDAT. The MDAT has been evaluated in 1426 healthy Malawian children as well as children with neurodisability (*n* = 80) or with severe wasting (*n* = 120) [23]. In this evaluation, sensitivity was 97%, and 18% of healthy children failed, translating to specificity of 82% [23]. These results show that the MDAT is an appropriate tool for assessing child development in Malawi.

The MDAT will be used at discharge (*t*
_*5*_) and 6 months later (*t*
_*6*_) to examine development in four domains: gross motor, fine motor, language, and social development [23]. Children will be given a pass or fail depending on their ability to complete increasingly advanced items on the MDAT [23]. The sum of passed items can be calculated and translated to age-specific *z* scores based on healthy Malawian children as reference standards [23].

### Secondary outcomes

Data will be collected at three time points: at enrollment (–*t*
_*1*_), discharge from hospital (*t*
_*5*_), and 6 months after discharge (*t*
_*6*_). All outcomes and measures are described in Table 1.

**Table 1 Tab1:** Primary, secondary, and implementation outcomes and measures

Outcomes	Measures
Primary outcome	
Child development: gross motor, fine motor, language, and social development (*t* _*6*_)	Malawi Developmental Assessment Tool (MDAT)
Secondary outcomes (child)	
Nutritional status (*t* _*6*_)	Mid-upper arm circumference (MUAC) Weight-for-length or -height *z* scores (WLZ or WHZ) Presence of bilateral pitting oedema Height-for-age *z* scores (HAZ)
Dietary intake (*t* _*6*_)	24-h dietary recall
Readmission to hospital (*t* _*5*_–*t* _*6*_)	Record of readmission to hospital for severe acute malnutrition (SAM)
Mortality (*–t* _*1*_ to *t* _*5*_ or *t* _*5*_–*t* _*6*_)	Death of child confirmed
Secondary outcomes (primary caregiver and household)	
Mental health status (*t* _*6*_)	Self-Reporting Questionnaire-20 (SRQ-20)
Nutritional status (*t* _*6*_)	Mid-upper arm circumference (MUAC) Body mass index (BMI)
Knowledge, attitudes, and practices (*t* _*6*_)	Questionnaire about hygiene and sanitation, nutrition and feeding, and malnutrition 24-h dietary recall of child
Stimulus and support for children in the household (*t* _*6*_)	Home Observation of the Measurement of the Environment (HOME) Inventory
Implementation outcomes	
Participant engagement (*t* _*1*_)	Number of enrolled participants who attend day 1 of the Kusamala Program
Participant adherence (*t* _*1*_–*t* _*4*_)	Number of enrolled participants who attend all 4 days of the Kusamala Program
Fidelity of the intervention programme	Assessment form of Kusamala Program delivery
Participant knowledge and attitudes of intervention content (*t* _*5*_)	Questionnaire about hygiene and sanitation, nutrition and feeding, and malnutrition

Important child outcomes are the nutritional status assessed by anthropometry (i.e. MUAC, WLZ or WHZ, oedema, and height-for-age *z* scores) and dietary intake based on a locally adapted 24-h dietary recall which will be performed only at follow-up (*t*
_*6*_) [32, 33]. Readmission to hospital and mortality at any time point are other secondary outcomes of interest. Child co-variates that will be considered include sex, age, and HIV status.

There are important co-variates in relation to households and primary caregivers measured at enrolment (–*t*
_*1*_) that could influence the ability of primary caregivers to care for their children during hospital treatment and in the home, and both are known to influence child outcomes [12, 18, 34]. First, the mental health status of primary caregivers will be measured with the Self-Reporting Questionnaire, which has been translated and validated for use in Malawi [35, 36]. Maternal depressive symptoms have been shown to be significantly associated with adverse outcomes in infants such as cognitive and socioemotional problems [12, 18, 34]. Furthermore, nutritional status of primary caregivers according to two anthropometric outcomes, body mass index and MUAC, will be assessed. Other measured co-variates that could influence child outcomes include HIV status, age, education level, and marital status of the primary caregiver as well as location (i.e. urban or rural) and monthly income of the household, for example.

Primary caregiver outcomes of interest at 6 months (*t*
_*6*_) will also include mental health status, nutritional status, as well as knowledge, attitudes, and practices relating to malnutrition, nutrition and feeding, and WASH based on the WHO *Indicators for assessing infant and young child feeding practices* [33]. Lastly, the environment in the home will also be assessed at follow-up 6 months after discharge (*t*
_*6*_) using an adapted and translated version of the Home Observation of the Measurement of the Environment (HOME) Inventory [37]. The HOME Inventory includes observations and interview questions to the primary caregiver to establish the amount and quality of interaction and input in the child’s home environment; this may be related to developmental outcomes in children [11, 37].

### Implementation outcomes

Participant engagement and adherence to the Kusamala Program will be evaluated based on the proportion of participants that attend the first day of the programme (*t*
_*1*_) and the number of participants that attend all 4 days of the programme (*t*
_*1*_–*t*
_*4*_), respectively. Fidelity of 20% of the intervention sessions will be assessed using a tool designed to capture duration of sessions, delivery of specific intervention content, and counselling skills according to the WHO Care for Child Development Package [29]. Following the intervention, knowledge and attitudes of primary caregivers who participate in the Kusamala Program will be demonstrated with the use of a questionnaire at discharge from hospital and at follow-up.

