### Objectives and hypothesis

The primary objective of the trial is to evaluate the effects of a 4-day hospital-based intervention for primary caregivers of children with SAM on child development and nutritional status after 6 months.

The secondary objective is to understand the effects of this programme on knowledge, attitudes, and practices, as well as mental health status of primary caregivers.

The hypothesis is that the intervention programme for primary caregivers will improve developmental and nutritional outcomes in children hospitalized with SAM.

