**Fig. 2 Fig2:**
[figure not shown]
Modified version of the CONSORT 2010 flow diagram

Data will be analysed using the statistical software Stata 14, R v3.2.5, and WHO Anthro v3.2.2 for anthropometric *z*-score calculations [43–45]. Missing data will be accounted for depending on the nature of drop-outs and loss to follow-up.

Descriptive statistics will be performed to summarize baseline characteristics of participants in both the intervention and comparison groups. More specifically, means and SD will be calculated for continuous variables such as the age of children, whereas the number of participants and percentages will be calculated for categorical variables such as the presence of oedema.

MDAT *z* scores standardized by age and based on a reference population of Malawian children will be calculated [23]. *Z* scores of each domain will be analysed separately to understand if the intervention influences certain domains more than others and a composite score of overall child development will be calculated if statistically appropriate. Upon completion of data collection for the internal pilot study, the variance of the primary outcome, child development using the MDAT, will be determined. The variance will be used to recalculate the sample size for the full trial [25, 26].

To determine the effect of the intervention on the primary outcome measures and continuous secondary outcomes, analysis of co-variance (ANCOVA) will be conducted to determine if there are differences between the intervention groups and the comparison groups while allowing for adjustment of co-variates in the analysis [46].

Multiple logistical regression will be performed to determine whether the intervention influenced binary outcomes such as the presence or absence of oedema. Subgroup analyses will be performed with participant age categories (i.e. infants and older children) and types of SAM (i.e. marasmus and kwashiorkor), and neurodisability, since children with neurodisability such as cerebral palsy are included in this study.

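### The discharge knowledge questionnaire is assigned to programme caregivers and nowhere to comparison caregivers, although a questionnaire of the same description is the 6-month between-arm outcome; giving it to both arms removes an avoidable risk of bias

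*Protocol article*

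**What the plan says.** The article's Objectives and hypothesis section states: "The secondary objective is to understand the effects of this programme on knowledge, attitudes, and practices, as well as mental health status of primary caregivers".

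Table 1 (Secondary outcomes section) has two rows that matter here.

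- **Secondary outcome, 6 months after discharge (t6).** Caregiver knowledge, attitudes and practices are measured by "Questionnaire about hygiene and sanitation, nutrition and feeding, and malnutrition 24-h dietary recall of child". The text below the table describes this outcome as "knowledge, attitudes, and practices relating to malnutrition, nutrition and feeding, and WASH based on the WHO" indicators for infant and young child feeding.
- **Implementation outcome, discharge (t5).** "Participant knowledge and attitudes of intervention content" is measured by "Questionnaire about hygiene and sanitation, nutrition and feeding, and malnutrition".

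The Implementation outcomes section then says whose discharge scores are meant: those of "primary caregivers who participate in the Kusamala Program will be demonstrated with the use of a questionnaire at discharge from hospital and at follow-up".

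On analysis, the Statistical analysis section says: "To determine the effect of the intervention on the primary outcome measures and continuous secondary outcomes, analysis of co-variance (ANCOVA) will be conducted". A knowledge score at t6, if treated as continuous, falls under that between-arm comparison.

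**The concern.** The t6 comparison should differ between arms only through the programme. If programme caregivers answer a set of questions at discharge and comparison caregivers do not, the arms also differ in prior exposure to the test. Having seen the questions can help recall, or signal which topics the study team cares about. Such an effect would add to any programme effect. It would coincide completely with allocation, so adjusting for covariates in the ANCOVA could not separate the two.

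At stake is the knowledge and attitudes part of the secondary objective. There is also a practical side: a form used in one arm only can tell whoever administers it which arm the caregiver is in.

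**Working it through.** No figure in the article depends on this point, so the main check is to set the sections side by side.

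**1. Who gets the form at discharge?** The sentence under Implementation outcomes is the only text that says, and it names programme caregivers. The other measures in that section (attendance on day 1, attendance on all 4 days, fidelity of sessions) can apply only to the intervention arm. In Table 1 the neighbouring rows use the word participant for people attending the programme, and the t5 row is about knowledge of the intervention's content. The general statement that data are collected at enrolment, discharge and 6 months has no arm restriction, but it refers to Table 1 for detail. There the questionnaire at t5 appears only in the implementation block.

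**2. Is it the same questionnaire?** Table 1 uses identical words for the instrument at t5 and t6; the t6 row adds a 24-hour dietary recall. The Implementation outcomes sentence refers to one questionnaire at both times. The instrument is not shown, so identity of items is likely but not established.

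**3. Is t6 compared between arms?** Yes, on the secondary objective and the Statistical analysis section read together.

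**4. Could adjustment help?** No enrolment knowledge score is named among the caregiver covariates (that list is given by example). Such a score would not remove the problem anyway, because the extra exposure comes after randomisation and in one arm only.

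**5. Who administers the form?** The Data collection and management section gives data collection, including assessments at discharge, to three enumerators. The Biostatistics procedure and blinding section says those doing data collection are blinded and exempts the nurses. If enumerators give the form to one arm only, those sections conflict with the Implementation outcomes sentence. If nurses give it, they do not.

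**Illustration of size (assumption only).** Inputs: n = 160 per arm and α = 0.05 two-sided (Sample size calculation section); true programme effect 0; a one-arm testing effect of b SD at t6, for which the documents give no value, taken as 0 to 0.3.

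Standard error of the difference in SD units: √(2/160) = 0.1118.

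Probability of a significant result = [1 − Φ(1.96 − b/0.1118)] + Φ(−1.96 − b/0.1118).

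| b (SD) | b/0.1118 | Probability |
|---|---|---|
| 0 | 0 | 0.050 |
| 0.05 | 0.447 | 0.073 |
| 0.1 | 0.894 | 0.145 |
| 0.2 | 1.789 | 0.432 |
| 0.3 | 2.683 | 0.765 |

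A two-sample t-test gives 0.763 in the last row, hence about 76%. With 120 per arm, to allow for losses, the last four rows become 0.067, 0.121, 0.341 and 0.642. Clustering is ignored. With groups of four and the article's intracluster correlation of 0.001, the design effect is 1 + 3 × 0.001 = 1.003, which changes nothing visible; that correlation was, however, chosen for the developmental outcome and not for caregiver knowledge.

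**The case against.** The strongest reply is that the article never says the form is withheld from the comparison arm. The sentence covers discharge and follow-up together. If it excluded comparison caregivers it would exclude them at follow-up too, which contradicts Table 1. It may therefore say only whose scores are reported as evidence of uptake. The unrestricted data-collection schedule and the blinding of data collectors also fit a form given to both arms. Which form goes to whom at each visit is, besides, often left to a fuller protocol.

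Part of this stands. That only programme caregivers complete the form is an inference, and so is the identity of the two instruments. But the reply does not remove the asymmetry. Table 1 separately makes t6 a between-arm outcome, whereas nothing places a comparison caregiver in front of the questionnaire at t5. Nor is this a mere omission: the article makes a positive statement about who is assessed at discharge, and that statement creates the difference.

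A reader might infer more than the documents support, in three ways:

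- **That the secondary objective is biased.** The documents show how bias could arise, not that it does. One sitting about 6 months earlier may leave almost no trace, and nothing says the answers are fed back to caregivers.
- **That the false-positive rate is somewhere near 76%.** That figure is the power formula applied to an assumed effect. Zero lies within the assumed range.
- **That the discharge score is invalid because it has no comparator.** The article does not claim that it shows change. A descriptive score in attendees, beside attendance and fidelity, is legitimate. A comparator would make it more informative, which is a gain and not the repair of an error.

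**Conclusion.** The point holds in a limited form. As worded, the plan gives the discharge questionnaire to one arm and uses a questionnaire of the same description to compare the arms at t6. If it is carried out that way, the t6 comparison of knowledge and attitudes can be biased, most plausibly in the programme's favour. This rests on two inferences, that comparison caregivers do not complete the form at discharge and that the items overlap, and on a testing effect of unknown size that may be negligible.

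The reach is narrow. Reported practices and the dietary recall are less exposed than knowledge items. The caregiver mental-health outcome and the primary MDAT outcome are untouched by the testing effect. Possible unblinding of data collectors is a separate consequence and depends on who administers the form. This is a cheap improvement to a secondary outcome and no threat to the trial's main conclusion.

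**What to change.** In the Implementation outcomes section and in Table 1, state that caregivers in both arms complete the t5 questionnaire, at the same point of the discharge visit relative to the roughly 15-minute discharge counselling on nutrition and WASH. Report the t5 score by arm. If that is not feasible, either drop the questionnaire at t5 or use different items at t5 and t6. If both arms already complete it, one sentence saying so is enough.

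The Trial status section says recruitment began in November 2016 and was expected to run to mid-2019, so some caregivers may already have been discharged under the present wording. The date of any change should be recorded. The t6 comparison could then be repeated in groups discharged after it; groups are randomised week by week, so that subset remains a randomised comparison.

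The cost is about 160 extra short questionnaires, one per comparison caregiver at the planned minimum size, at a visit where participants are already assessed. No new staff or instrument is needed. The downside is a few more minutes for comparison caregivers and perhaps a slight prompting effect, but that would then be equal in both arms.

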### Sample size calculation

The sample size estimate is based on cross-sectional study data of development of children with SAM at discharge from the NRU using the MDAT [38]. Results from this study showed that, based on MDAT *z* scores, the variance for gross motor was 1.9 SD, for fine motor was 1.2 SD, and for language was 1.7 SD [38]. Therefore, the composite variance for those domains was 1.6 SD. This was used to calculate the sample size using α = 0.05 and 80% power, an estimated intracluster correlation coefficient of 0.001, and with an expected effect size of 0.5 using Cohen’s *d* [39, 40]. With this approach, the initial estimate of the sample size for the primary outcome is a minimum of 160 primary caregiver-child pairs per arm (*n* = 320). As discussed previously, an internal pilot study will be conducted to determine the variance of the primary outcome in the first 15 children in each study group at 6 months post-discharge from hospital which will be used to recalculate the sample size [25].

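### A Cohen's d of 0.5 does not give 160 per arm; that size fits a raw difference of 0.5 MDAT z units with SD 1.6 (d about 0.31), and the planned recalculation depends on which is meant

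*Protocol article*

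**What the plan says.** The protocol article, Sample size calculation, takes MDAT z-score spreads from a cross-sectional study of children with SAM at discharge: 1.9 for gross motor, 1.2 for fine motor and 1.7 for language. It then says "the composite variance for those domains was 1.6 SD". The next sentence makes this figure an input: "This was used to calculate the sample size using α = 0.05 and 80% power". The other inputs are "an estimated intracluster correlation coefficient of 0.001, and with an expected effect size of 0.5 using" Cohen's *d*. The result is that "the initial estimate of the sample size for the primary outcome is a minimum of 160 primary caregiver-child pairs per arm", 320 in all.

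No raw difference in z units, sidedness, dropout allowance or multiplicity adjustment is stated. Trial overview and design gives an average weekly group of four pairs, and the Abstract gives a maximum of six.

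The size is to be revisited. The same section, Trial overview and design, and Statistical analysis all provide for an internal pilot that estimates the variance of the MDAT score. Statistical analysis adds: "The variance will be used to recalculate the sample size for the full trial".

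**The concern.** Cohen's *d* is a difference already divided by the standard deviation. With *d* set at 0.5, the sample size follows from α, power and the design effect alone, and no SD enters. The section nevertheless says the 1.6 was used. The two statements cannot both describe the calculation that produced 160.

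Two things are at stake. First, the reader cannot tell which effect the trial is powered for: half a sample SD (0.8 z units if the SD is 1.6) or 0.5 z units (about a third of a sample SD). Second, the recalculation from pilot variance behaves differently under the two. With a fixed standardised effect, the pilot variance has no influence on the sample size. With a fixed raw difference, the sample size grows with the square of the SD.

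**Working it through.** **Inputs.** α = 0.05, 80% power, ICC 0.001, effect 0.5, spread 1.6 and 1:1 allocation (Sample size calculation); average group of 4 (Trial overview and design), maximum 6 (Abstract). Two-sided testing is my assumption. The spread is the plain mean of the domain figures: (1.9 + 1.2 + 1.7)/3 = 4.8/3 = 1.6.

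**Formulae.** Per arm, n = 2(1.960 + 0.842)² × SD²/Δ² = 2 × 7.849 × SD²/Δ². The two-sample t-test solution is about one higher. Design effect DE = 1 + (m − 1) × 0.001, which is 1.003 for m = 4 and 1.005 for m = 6.

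**Reproducing 160.** Take Δ = 0.5 z and SD = 1.6, so d = 0.5/1.6 = 0.3125.
- Normal approximation: 2 × 7.849 × 2.56/0.25 = 160.7; × 1.003 = 161.2.
- t-test: 161.7; × 1.003 = 162.2.
- Rounded up, 161 to 163 across the approximations and design effects, within 2% of 160.

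**The inputs as worded.** Take d = 0.5.
- Normal approximation: 2 × 7.849/0.25 = 62.8, so 63.
- t-test: 63.8, so 64.
- With the design effect, 63 to 65. One-sided testing would give 50 to 51.

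**Power at 160 per arm**, from Φ(d√(n/2) − 1.960) with √80 = 8.944.
- d = 0.3125: Φ(2.795 − 1.960) = Φ(0.835) = 79.8% (t-test 79.6%).
- d = 0.5: Φ(4.472 − 1.960) = Φ(2.512) = 99.4%.

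**Could something else bridge 64 to 160?**
- Clustering: the DE would have to be 160/63 = 2.54, so an ICC of 1.54/3 = 0.51 (m = 4) or 1.54/5 = 0.31 (m = 6), against the stated 0.001.
- Attrition: 1 − 64/160 = 60%.
- Bonferroni over 2 to 4 domains: 77 to 91 per arm.
- 90% power: 85 per arm.

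None of these is both stated and large enough.

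**Effect on the recalculation (t-test, two-sided, 80% power, before the design effect).**

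| Pilot SD | n per arm, d held at 0.5 | n per arm, raw 0.5 z held | Power at 160 for 0.5 z |
|---|---|---|---|
| 1.6 | 64 | 162 | 79.6% |
| 1.8 | 64 | 205 | about 70% |
| 2.0 | 64 | 253 | about 61% |

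**The case against.** The best defence is that 160 is a sound number. It gives essentially the planned power for a raw 0.5 z difference and far more than that for d = 0.5, so a reader who infers that the trial is under-sized would be wrong. This stands.

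The label also has a partial explanation. MDAT z scores are scaled to healthy Malawian reference children, so 0.5 z is half a *reference* SD. That makes the slip understandable. It does not make it Cohen's *d* in a sample whose SD is taken as 1.6.

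A reader might take *variance* literally, set SD = √1.6 = 1.265, and get 2 × 7.849 × 1.6/0.25 = 100.5, or 101 to 102 per arm. The text gives this little support: SD is printed beside every figure, and 160 itself fits 1.6 only as an SD. *Variance* is loose wording for spread.

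A reader might also infer that the recalculation will cut the trial to 64 per arm, leaving about 42% power for a 0.5 z difference. The protocol plans no such cut, and it calls 160 a minimum. A team repeating the calculation that produced 160 would respond to the pilot SD. The cut is the worst case of following the words literally.

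Finally, other routes reach about 160: one-sided α with SD 1.6 and 20% dropout gives 159; a variance of 1.6 with 37% dropout gives 161. Both need a dropout allowance that the protocol does not state. The claim that only one reading fits is therefore limited to the stated inputs.

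**Conclusion.** The point holds as an inconsistency between the stated effect size and the stated sample size. As worded, the inputs need about 64 per arm, against 160 stated, a ratio of 2.5. Among the stated inputs, only a raw difference of 0.5 z with SD 1.6 reaches 160.

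This rests on two-sided α, no unstated dropout or multiplicity allowance, and a comparison of two means. The raw-difference reading is a strong inference, not a statement in the protocol, so the sponsor should confirm it.

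The documents do not support a claim that initial enrolment is wrong or that a reduction is planned. What needs correcting is the effect label, the word *variance*, and the missing statement of which target the recalculation holds fixed. The last is the most important, because the protocol commits to a recalculation whose result depends on it.

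**What to change.** Ask the sponsor to confirm which effect was used. If it was the raw difference, restate the paragraph: SD of 1.6 MDAT z units, target difference of 0.5 z units (Cohen's *d* about 0.31), two-sided α of 0.05 if that is what was used, ICC 0.001, and about 80% power at 160 per arm. Replace *variance* with *standard deviation* wherever the figures are SDs.

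In the internal-pilot recalculation, state that the raw difference of 0.5 z is held fixed and only the SD is updated.

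The cost is the wording of one paragraph and one sentence, with no change to the initial enrolment target. It should be done before the recalculation is run.

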## Background

### The global burden of malnutrition

Worldwide, malnutrition is a direct or indirect cause of an estimated 45% of all child deaths [1]. Severe acute malnutrition (SAM) is one type of malnutrition that manifests in two forms: marasmus, identified by severe wasting; and kwashiorkor, characterized by the presence of bilateral pitting oedema [2]. Morbidities such as pneumonia, human immunodeficiency virus (HIV), or diarrheal disease often complicate effective management of SAM and are associated with increased mortality [1, 3–5]. Children with SAM are often admitted to hospital due to serious illness rather than malnutrition alone. Mortality in hospitalized children with SAM can be up to 35% even when World Health Organization (WHO) protocols are followed [4, 5].

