### Trial overview and design

This study will evaluate a comprehensive structured intervention package for primary caregivers of children aged 6 to 59 months hospitalized with SAM. It will be a pragmatic trial aimed at replicating how this type of intervention could be delivered in a real nutrition rehabilitation unit (NRU) setting and its effectiveness in this setting [22]. The primary outcome is child development, which will be assessed using the Malawi Developmental Assessment Tool (MDAT), a locally adapted and validated tool for evaluating multiple domains of child development (i.e. gross motor, fine motor, language, and social domains) [23].

The design of the study is a cluster-randomized controlled trial (superiority design) that will be conducted at the Moyo NRU of the Queen Elizabeth Central Hospital in Blantyre, Malawi (NCT03072433). A cluster-randomized controlled trial design was selected because the intervention is most feasible if delivered to groups of primary caregivers rather than individual caregivers. This design will also prevent temporal overlap between the two study arms: 1) an intervention arm of primary caregivers and children with SAM participating in an intervention programme; and 2) the comparison arm of primary caregivers and children with SAM receiving standard care. All other clinical and nutritional aspects of care will be equivalent; children will be treated per hospital protocol and WHO guidelines [24]. One day of each week will be used to recruit and enrol an estimated average of four primary caregiver-child pairs. Once formed, the group will be randomly assigned to either the intervention or comparison arm. Recruitment and enrolment will not overlap with the delivery of intervention sessions, although it is possible that children from different groups will be in the NRU at the same time depending on the duration of their in-patient treatment.

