### Data collection and management

Data collection will be performed by three different enumerators who have been trained on all relevant assessment tools and questionnaires, including the MDAT. Baseline data collection will take place over approximately 80-week-long cycles, depending on enrolment rates, with assessments performed at enrolment (–*t*
_*1*_) and at discharge (*t*
_*5*_). These data collections will be done privately in the NRU, either in the procedures room or in the back bay depending on availability of these locations. Home visits will be conducted for follow-up assessments 6 months after children are discharged from hospital (*t*
_*6*_) over the course of 80 weeks. For participants who prefer not to be visited in the home, they will be asked to come back to the NRU for follow-up assessments.

Investigators will maintain medical and research records for this trial in compliance with regulatory and institutional requirements for the protection of confidentiality of subjects. All personnel with access to data and information related to this trial will take all reasonable precautions to maintain the confidentiality of information. Data will be collected using paper forms which will be kept in a locked filing cabinet and will be accessed only by the investigators. Data entry will be performed into a Research Electronic Data Capture database, which includes automated checks for data values with coded numbers [41]. De-identified data will be exported in a password-encrypted file.

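### The 160 per arm leaves no room for death or loss before the 6-month outcome, and the planned recalculation is fed only by the variance

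*Protocol article*

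**What the plan says.** All places are in the protocol article.

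- **Sample size calculation** gives the inputs: "This was used to calculate the sample size using α = 0.05 and 80% power"; "Therefore, the composite variance for those domains was 1.6 SD"; "an estimated intracluster correlation coefficient of 0.001"; and "with an expected effect size of 0.5", labelled as Cohen's d. From these, "the initial estimate of the sample size for the primary outcome is a minimum of 160 primary caregiver-child pairs per arm" (n = 320). No term for death or loss appears.
- **Trial overview and design** uses one day a week to "recruit and enrol an estimated average of four primary caregiver-child pairs". The Abstract allows up to six.
- **Data collection and management**: "Baseline data collection will take place over approximately 80-week-long cycles", subject to enrolment rates. Follow-up visits also run over 80 weeks.
- **Trial status** has recruitment running from 28 November 2016 to about mid-2019.
- **Primary outcome** is the MDAT 6 months after discharge, so only children alive and reached at that point contribute.
- **Table 1** lists child mortality, both before discharge and between discharge and 6 months, as a secondary outcome. **Statistical analysis** foresees drop-out and loss to follow-up.
- **The global burden of malnutrition**: "Mortality in hospitalized children with SAM can be up to 35% even when World Health Organization (WHO) protocols are followed".
- **Trial overview and design**, **Sample size calculation** and **Statistical analysis** each name the variance of the MDAT as what the internal pilot passes to the sample size recalculation. The pilot also records adherence and engagement, which concern session attendance, not 6-month retention.

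**The concern.** The number that the formula requires with a measured outcome looks the same as the number to be enrolled. Enrolment takes place in hospital, soon after admission, among severely ill children, and the outcome is read 6 months after discharge. The protocol itself expects some children to die or be lost in between. If the calculated number is also the enrolment target, every lost child takes power below the stated 80%, and a null result would be read as better powered than it was. The recalculation is the natural place to correct this, but its only stated input is the variance.

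**Working it through.** **Inputs.** Alpha 0.05, power 80%, SD 1.6, effect 0.5 and ICC 0.001 come from Sample size calculation. The average group size of 4 comes from Trial overview and design. Sidedness is not stated. The 1.6 is called a variance but is the mean of three values given in SD units: (1.9 + 1.2 + 1.7)/3 = 1.6.

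**Step 1: reproduce 160.** Two-sided test, raw difference 0.5, SD 1.6:

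n per arm = 2 × SD² × (1.960 + 0.842)² / 0.5² = 2 × 2.56 × 7.849 / 0.25 = 160.7

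Design effect = 1 + (4 − 1) × 0.001 = 1.003, giving 161.2. The t-based version gives 161.7, or 162.2 with the design effect. This matches 160 to within two or three children, with every child analysed. The standardised effect is 0.5/1.6 = 0.3125.

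**Step 2: try the other readings.** Each includes the design effect and no loss. The last column is the allowance that would have to sit inside 160, 1 − n/160.

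| Reading | n per arm | Implied allowance |
|---|---|---|
| Raw 0.5, SD 1.6, two-sided | 161 | none |
| Raw 0.5, SD 1.6, one-sided | 127 | 21% |
| Raw 0.5, variance 1.6 (SD 1.265), two-sided | 101 | 37% |
| Raw 0.5, variance 1.6, one-sided | 80 | 50% |
| Cohen's d 0.5, two-sided | 63 | 61% |
| Cohen's d 0.5, one-sided | 50 | 69% |

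Only the first returns 160 without adding a loss rate that the article does not state.

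**Step 3: compare with enrolment.** 80 weekly groups × 4 pairs = 320 = 2 × 160. Against this, 28 November 2016 to the end of June 2019 is about 135 weeks. At four pairs a week that is 135 × 4 = 540; 320 pairs over 135 weeks is 2.4 a week. The two descriptions do not agree.

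**Step 4: power if 160 per arm are enrolled.** Two-sample t-test, d = 0.3125, effective n = 160 × (1 − loss) / [1 + (4 × (1 − loss) − 1) × 0.001]:

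| Death plus loss | Assessed per arm | Power |
|---|---|---|
| 0% | 160 | 79.5% |
| 10% (assumed) | 144 | 75% |
| 20% (assumed) | 128 | 70% |
| 30% (assumed) | 112 | 64% |
| 35% (background upper bound) | 104 | 61% |

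The normal approximation gives values 0.2 to 0.4 percentage points higher.

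**Step 5: enrolment needed to keep 160 assessed.** 160/(1 − loss) is 178 per arm at 10%, 200 at 20%, 229 at 30% and 247 at 35%. At four pairs a week, 20% loss means 400 pairs, or 100 weekly groups.

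**The case against.** Four points on the other side deserve weight.

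1. **The enrolment total is not fixed at 320.** The article does not say whether 160 means enrolled or assessed, and it calls the figure initial and a minimum. The four pairs and the 80 cycles are both approximate. Groups of six would give 80 × 6 = 480, and 135 weeks at four a week would give 540, more than the 494 (2 × 247) needed at 35% loss. This stands: a reader might infer that the plan assumes every enrolled child survives and is assessed, but the text does not establish that. The longer window could equally reflect slower accrual, so it does not show a planned allowance either.

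2. **The shortfall depends on the effect-size reading.** With a literal Cohen's d of 0.5, about 64 per arm suffice (t-based), and 160 enrolled keep about 95% power even at 35% loss. A one-sided test, or 1.6 taken as a true variance, would also leave room. This stands as a condition. None of these readings yields 160 from the stated inputs, so none rescues the calculation as published.

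3. **The 35% is not a trial forecast.** It is tempting to say that power fails under the article's own mortality figure. The figure is a background upper bound for hospitalised children. The trial excludes children judged likely to die within 6 months, enrols on one day a week so that some early deaths precede enrolment, and plans home visits. The 61% is therefore an outer bound.

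4. **The size is provisional and the article is condensed.** A full protocol may provide for retention, so one cannot say that retention will never be considered. What the article does state is the input to the recalculation, in three places, and it is the variance each time.

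**Conclusion.** The concern holds in a conditional form. The only reading that reproduces 160 from the published inputs alone contains no allowance for death or loss, so this is more than an omission of detail from a condensed article. If about 320 pairs are enrolled, power starts at 79.5% and falls to about 75%, 70% and 64% at losses of 10%, 20% and 30%. Those rates are assumptions, because the article gives no expected loss rate for the trial. The conclusion also rests on 0.5 being a raw z-score difference on SD 1.6 and on a two-sided test. The formula itself is not miscalculated. The weakness is that the calculated number appears to serve as the enrolment number, in a plan that expects deaths and losses, with a recalculation that does not name retention as an input.

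**What to change.** 1. Settle first what 0.5 and 1.6 mean (raw difference or Cohen's d, SD or variance) and state the sidedness. The remaining steps assume the reading that gives 160.
2. State that 160 per arm is the number of children with an MDAT at 6 months.
3. Give the enrolment target explicitly, and reconcile about 80 weekly groups of four with recruitment lasting until mid-2019.
4. Restate power for 320 enrolled over a stated range of death plus loss, as in the table above.
5. Add 6-month retention observed in the internal pilot, pooled over arms, to the recalculation: N enrolled = N evaluable / (1 − loss). Pooling keeps this blinded. With as few as 30 pairs in the pilot the rate will be imprecise, so a range should accompany it.

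The cost is a less favourable stated power, one further input to a recalculation already planned, and possibly a larger target with longer recruitment.
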